## Abstract

Spatial navigation (SN) has been reported to be one of the first cognitive domains to be affected in Alzheimer’s disease (AD), which occurs as a result of progressive neuropathology involving specific brain areas. Moreover, the epsilon 4 isoform of apolipoprotein-E (APOE-ε4) has been associated with both sporadic and familial late-onset AD, and patients with mild cognitive impairment (MCI) due to AD are more likely to progressively deteriorate. Spatial navigation performance will be examined on a sample of 76 community-dwelling senior citizens (25 healthy controls; 25 individuals with subjective cognitive decline (SCD); and 26 patients with MCI due to AD) via a virtual computer-based task (i.e., the AppleGame) and a naturalistic task (i.e., the Detour Navigation Test—modified version) for which a wearable device with sensors will be used for recording gait data and revealing physiological parameters that may be associated with spatial disorientation. We expect that patients with MCI due to AD and APOE-ε4 carriers will show altered SN performances compared to individuals with SCD and healthy controls in the experimental tasks, and that VR testing may predict ecological performance. Impaired SN performances in people at increased risk of developing AD may inform future cognitive rehabilitation protocols for counteracting spatial disorientation that may occur during elders’ traveling to unfamiliar locations. The research protocol has been approved by the Ethics Committee of the Istituto Auxologico Italiano. Findings will be published in peer-reviewed medical journals and discussed in national and international congresses.

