### 1.4. Genetic Risk Factors for Alzheimer’s Disease: Role of the Apolipoprotein-E [APOE]

Beyond increasing age, the ε4 allele of the apolipoprotein-E gene represents the most important risk factor for AD, providing an opportunity for assessing subclinical alterations of behavior at very early disease stages. APOE is centrally involved in lipoprotein metabolism and other biological functions [48]. ApoE-lipoproteins are involved in lipids transport into bloodstream, and they also bind to hydrophobic amyloid-β (Aβ) peptide, which is thought to initiate toxic events that lead to synaptic dysfunction and neurodegeneration in AD [49]. APOE genotype is determined by three main alleles, ε2, ε3 and ε4, resulting in six possible combinations (i.e., ε2/2, ε2/3, ε2/4, ε3/3, ε3/4, and ε4/4). Population frequency of the ε4 allele is approximately 14%, the ε2 allele 6%, and the ε3 allele 78% [50]. The presence of the ε4 allele is associated with an increased risk of cognitive decline during normal aging [50]. The APOE-ε4 allele is also an established risk factor for neurodegenerative conditions, such as AD [51,52] as opposed to the ε2 allele that offers protection against the disease [53,54]. Individuals carrying one APOE-ε4 allele are at threefold increased risk and those carrying two ApoE-ε4 alleles are at more than tenfold increased risk of developing AD [47]. Remarkably, cognitively normal subjects who are homozygous for the ε4 allele have reduced glucose metabolism in the same regions of the brain as in patients with probable AD [55].

In a previous investigation using a VR test (i.e., The AppleGame), we provided evidence of a specific deficit of PPI decades before potential disease onset in AD risk carriers, specifically when the recruitment of compensatory navigational strategies via supportive spatial cues from posterior cingulate/retrosplenial cortex was disabled [43].

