### 1.7. Aim of the Study Protocol

The first endpoint of the research is to explore differences in SN performances among healthy older adults, individuals with SCD, and patients with MCI due to AD on a VR task (i.e., the “AppleGame”) and on a naturalistic task (i.e., the Detour Navigation Test-modified version, DNT-mv) using an innovative technological apparatus recording gait data and revealing physiological parameters that may be associated with SD.

The second endpoint of the research is to verify if examinees’ performances in such a well-characterized laboratory-based SN-testing task may predict impairment in a real-world context.

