### 2.4. Statistical Analysis

Data distribution will be first checked on collected variables by assessing skewness and kurtosis values, by performing normality and heteroscedasticity tests, and by visually inspecting histogram and Q–Q plots. Based on data meeting or non-linear model assumption, either parametrical or non-parametrical analyses will be performed. By means of the R marco *pwr* [86], the minimal sample size has been set as 76 participant, based on a power analysis for a multiple regression model that took into account the following parameters: α = 0.05; 1-β = 0.9; *f*^2^ = 0.15 (medium effect size, in order to be conservative) [87]; and numbers of predictors: 3 (age, APOE genotypes, and belonging to each group, with the last two predictors as dummy variables).

We will detect the route disorientation scores, i.e., WTs and MsH, as already described in Puthysserypaddy et al. [64]. Accordingly, all the violations in terms of deviations from the pre-established return path (i.e., movement at an intersection onto a different path as compared to the original one, or non-roadable walkways) will be written down by the experimenter as WTs in a pre-set paper grid for *Route A*. The overlaps with the *Route A* return path, and, likewise, non-roadable walkways will be written down by the experimenter as WTs in a pre-set paper grid for Route *B*. Further, we will detect the MsH as the participant either slows down/stops and looks around to aid orientation or verbally admits to the experimenter that he/she is unsure about his/her whereabouts, both for *Route A* and the *Route B* return path.

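### The sample-size calculation counts three predictors, but three diagnostic groups make it at least four; at N = 76 the power is about 75%, not 90%

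*Protocol article*

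**What the plan says.** Protocol article, section 2.4 (Statistical Analysis), states that "the minimal sample size has been set as 76 participant", "based on a power analysis for a multiple regression model" run in the R package pwr. The inputs are "α = 0.05; 1-β = 0.9", a Cohen f² of 0.15 (described as a "medium effect size, in order to be conservative") and "numbers of predictors: 3 (age, APOE genotypes, and belonging to each group, with the last two predictors as dummy variables".

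The Abstract splits the sample into "25 healthy controls; 25 individuals with subjective cognitive decline (SCD); and 26 patients with MCI due to AD". The first endpoint in section 1.7 is to "explore differences in SN performances among healthy older adults, individuals with SCD, and patients with MCI due to AD". There are thus three groups, and the aim is to tell them apart.

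For APOE, section 2.4 speaks of genotypes without giving a coding. The only APOE contrast the article hypothesises is ε4 carriers against non-carriers (Abstract and Discussion).

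**The concern.** The predictor count in a regression power calculation is the numerator degrees of freedom: the number of coefficients tested, not the number of named factors. A factor with k levels needs k − 1 dummy variables, so group needs two. With age and a binary APOE term, a count of three leaves room for only one group coefficient.

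Two things are at stake. First, the justification for N = 76 rests on a wrong input, and the power claimed for the study is not the power it has. Second, anyone who corrects the power figure but keeps three predictors will again arrive at an N that is too small.

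**Working it through.** **Inputs.** α = 0.05, target power 0.90, f² = 0.15, three predictors and N = 76 (all section 2.4); three groups of 25, 25 and 26 (Abstract). *Assumption:* APOE enters as one binary term, carrier or non-carrier. No allowance for dropout is stated and none is applied.

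**Formula.** For the joint test of u predictors, v = N − u − 1 and the noncentrality is λ = f² × (u + v + 1) = f² × N. Power is P[F′(u, v, λ) > F₀.₉₅(u, v)], where F′ is the noncentral F distribution. This is the calculation pwr makes for regression.

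**Step 1: the plan's own figure, u = 3.** At N = 76, v = 72, λ = 0.15 × 76 = 11.4 and the critical F is 2.73; power is 0.796. Solving for 90% gives v = 94.48, so v + u + 1 = 98.48 and N = 99. The stated 76 is not reproduced. Solving for 80% gives v = 72.71, so v + u + 1 = 76.71, which is 76 if truncated and 77 if rounded up. The stated N therefore fits 80% power, not 90%.

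**Step 2: correct the count.** Age (1) + APOE carrier (1) + group (3 − 1 = 2) = 4.

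**Step 3: recompute with u = 4.** At N = 76, v = 71, λ = 11.4 and the critical F is 2.50; power is 0.747. For 90%, v = 102.56, so v + u + 1 = 107.56 and N = 108.

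| Predictors | Power at N = 76 | N for 80% | N for 90% |
|---|---|---|---|
| 3 (as stated) | 0.796 | 77 | 99 |
| 4 (group as two dummies) | 0.747 | 85 | 108 |

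**Step 4: split the shortfall.** From 0.90 to 0.796 is about 10 points; this is the mismatch between 76 and 90% power with three predictors. From 0.796 to 0.747 is about 5 points; this is the missing df. In participants at 90% power, the mismatch is 99 − 76 = 23 and the df error is 108 − 99 = 9.

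**Step 5: the test closest to the first endpoint.** That endpoint concerns group differences, not the joint test that also includes age and APOE. For a 2-df group test in the four-predictor model (v = 71) at partial f² = 0.15, power at N = 76 is 0.850 with λ = f² × N = 11.4. With pwr's convention, λ = 0.15 × (2 + 71 + 1) = 11.1 and power is 0.840. N for 90% is 88 with λ = f² × N.

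**The case against.** The strongest reply is that the sentence describes a power calculation, not a fitted model, and that its wording suits an ordinary reading: three conceptual predictors, with the categorical ones expanded into as many dummies as they need. On that reading the analysis model is sound. This stands as far as the analysis is concerned. It does not rescue the power calculation, where u must count coefficients.

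A reader might go further and infer that the plan codes group as one 0/1 dummy or a 0/1/2 score, so that the SCD contrast is lost or forced midway. The documents do not support this. A score is not a dummy variable; nothing states a single indicator; and the one-way ANOVA in section 2.4 keeps three subgroups apart, though it is specified only for gait parameters and the SSNC questionnaire.

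A reader might also take the six genotypes in section 1.4 ("resulting in six possible combinations") to imply five APOE dummies and eight predictors. That section is background, and the hypotheses are about carriers, so an eight-predictor calculation would rest on a coding the plan never proposes.

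It can fairly be added that the df error is the smaller of the two faults in the sentence, and that a 2-df group test still has about 84–85% power at N = 76. Both points are right, and the verdict reflects them.

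**Conclusion.** The point holds as an error in the sample-size calculation. The predictor count is one too low, and the stated 90% power is not delivered with three predictors or with four. For the joint test at N = 76, f² = 0.15 and α = 0.05, power is about 75% with the correct 4 df. The larger part of the gap comes from the mismatch between 76 and 90% power, the smaller part from the df.

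The figures assume a binary APOE term, f² = 0.15 for the test in question and complete data on all 76 participants. It is not established that the analysis will fail to separate SCD from the other groups. The importance is moderate: a figure the study relies on is wrong, and correcting it is cheap.

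**What to change.** In section 2.4:

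- Name the predictors as age, ε4 carrier (yes/no), an SCD dummy and an MCI dummy with healthy controls as reference, and give the count as four.
- For the first endpoint, test group on 2 df and report the MCI–healthy, MCI–SCD and SCD–healthy contrasts.
- Replace the 90% claim with the power at N = 76: about 75% for the joint 4-df test, and about 84–85% for the 2-df group test at partial f² = 0.15. If 90% is to be kept for the joint test, the N that goes with it is 108.

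Restating the power at N = 76 costs a sentence of wording, one recalculation and one residual df. It needs no new participants or data. Keeping 90% for the joint test would mean 108 − 76 = 32 more participants.

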## 2. Materials and Methods

### 2.1. Design, Study Population, Recruiting Centers and Trial Registration

This is a multi-center prospective observational study. A sample of outpatients with SCD and MCI due to AD will be enrolled from three sites in Lombardy (Italian Region): “San Gerardo” Hospital (Monza), “Luigi Sacco” University Hospital (Milan), and Fondazione IRCSS Ca’ Granda Ospedale Maggiore Policlinico (Milan, Italy).

Individuals with SCD will be detected according to Jessen and colleagues’ criteria [79] while prodromal AD will be defined according to Dubois and colleagues’ criteria [80], respectively. Healthy older adults will be enrolled through advertisements distributed in social centers for senior citizens in Milan (Italy) and through popular science events (conferences, webinars) concerning research in AD prevention. The three sites currently use the neuropsychological batteries reported in the Appendix A. Healthy older adults will be assessed by the experimenters at the Department of Psychology, Catholic University (Milan, Italy), by adopting the same neuropsychological battery as the IRCSS Ca’ Granda Ospedale Maggiore Policlinico (Milan, Italy). Family medical history of AD was collected during clinical interview along with laboratory tests results and neuroimaging findings for outpatients with SCD and MCI due toAD.

For the whole sample, inclusion criteria will involve the following: age from 65 to 85 years; education not less than 5 years; basic ICT skills. All participants will be excluded from the study according to the presence of visual, hearing, or motor impairment significantly interfering with SN tasks; neurological/psychiatric disease or other medical conditions preventing SN; history of alcohol or drugs addiction; intake of psychotropic drugs; and presence of dementia. Recruitment will end on 29 February 2024.

With the aim of obtaining results that can be generalized, sociodemographic and clinical features of the sample to be recruited will be analyzed among the research team members prior to the sample enrollment according to epidemiological studies carried out on the Italian elderly population, specifically including MCI patients [81,82,83] and individuals with SCD [84].

The Uniform Resource Locator for the clinical trial registration is the following one: https://classic.clinicaltrials.gov/ct2/show/NCT05944601 (identifier: NCT05944601) (accessed on 13 July 2023).

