### 2.2. Genetic and Psychological Evaluation

All participants will be genotyped for the APOE polymorphisms by collecting genetic material extracted from buccal brushes using the Gentra Puregene^®^ (40723, Hilden, Germany) specific assay. The collected samples will be analyzed in the Neuropathology and Clinical Neurobiology Laboratory of “San Giuseppe Hospital” in Piancavallo (Verbania, Italy), IRCCS Istituto Auxologico Italiano. All participants will be blinded towards APOE genotype.

Subjective strategies of SN and personal satisfaction for wearable technology will be evaluated via the Subjective Spatial Navigation Complaints (SSNC) questionnaire [35] and the Tele-healthcare Satisfaction Questionnaire (TSQ-WT) [85], respectively, which have previously undergone a back-translation process for Italian culture adaptation.

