In addition to the experimenter visually identifying and recording the frequency of the MsH with a stopwatch and a pre-set paper grid, we will measure this variable more objectively using the Howdy Senior integrated accelerometer. For this purpose, we will use the motion sensor of the sensorial body measuring the individual’s linear acceleration in the three axes (i.e., x, y, z). To segment the magnitude signals, according to Schaat et al. [88], we will adopt time intervals of 10 s, with an overlap of 5 s between subsequent intervals because a 10 s segment is sufficiently long to capture multiple steps during walking, thus revealing important behavioral changes. In this way, we will detect the MsH as a signal flattened along the three axes. Further, given that physiological parameters may alter depending on the MsH, we will also investigate the relationship between step variability and co-occurring time-dependent cardiac and respiratory parameters detected by the Howdy App, expressed as mean values, via Pearson’s correlation coefficients or their non-parametric equivalent (i.e., Spearman’s rank order correlation). Moreover, we will run a one-way ANOVA (or its non-parametric equivalent) to compare performances of the three subgroups on gait parameters collected through the Aptive app and the SSNC questionnaire. In order to explore potential association between specific neurocognitive functions and SN impaired abilities, Pearson correlations or their non-parametric equivalent (i.e., Spearman’s rank order correlation) will be further performed between the AppleGame/DNT-mv results and the neuropsychological tests used in the sending centers, especially visual–constructive skills and executive functions (see Appendix A). Given the difference of the neuropsychological battery used in the sending centers, we will group tests according to the primary cognitive domain involved and we will divide the scores obtained in a dichotomous way for each participant according to the reported cut-off values in the test manuals, i.e., 0 = pathological performance; 1 = normal performance.

Finally, a linear/generalized linear regression analysis will be run, taking into account the drop errors of the AppleGame subtasks—considered one at a time—as independent variables, and the total number of “wrong turns” (WTs)/total number of “moments of hesitation” (MsH) (in seconds) of the DNT-mv as dependent variables.

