The Howdy Senior system has been recently implemented by the “Aptive” App capable of recording GPS data during the naturalistic experiment. These data include “Time” as the number of minutes to complete the route; “Latitude”, “Longitude”, “Altitude”, and “Speed” as estimated by the body integrated accelerometer for calculating steps variability; and “Direction” corresponding to gait orientation with values ranging from 0° to 360°, where 0° corresponds to the north, 90° to the east, 180° to the south, and 270° to the west. Thanks to the Aptive App, a GPX tracking of participants’ body movements around the urban environment will be registered, too.

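### Wrong turns and by-eye moments of hesitation are scored live by the experimenter with no rater masking described, which leaves the visual hesitation score in particular open to expectation bias

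*Protocol article*

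**What the plan says.** **Scoring.** Section 2.4 of the protocol article assigns both real-world scores to the experimenter. Deviations on Route A "will be written down by the experimenter as WTs in a pre-set paper grid for" that route, and Route B is handled the same way. An MsH is counted when the participant slows or stops and looks around for orientation, or "verbally admits to the experimenter that he/she is unsure about his/her whereabouts". The recording method is given as "In addition to the experimenter visually identifying and recording the frequency of the MsH with a stopwatch and a pre-set paper grid". The same sentence adds an instrumented measure: "we will measure this variable more objectively using the Howdy Senior integrated accelerometer", with 10 s windows overlapping by 5 s and a flattened three-axis signal as the criterion.

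**Masking.** The one statement is in Section 2.2: "All participants will be blinded towards APOE genotype". Nothing is said about the person keeping the grid.

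**Who meets whom.** Section 2.1 says "Healthy older adults will be assessed by the experimenters at the Department of Psychology", while SCD and MCI participants are outpatients enrolled from three hospital sites. Section 2.3.2 has the experimenter and a staff of clinical psychologists accompany each participant in the garden.

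**Expectation.** Section 3 predicts more WTs and MsH in MCI than in the other two groups.

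**Other recordings.** The text after Table 1 says that a GPX track of participants' "body movements around the urban environment will be registered". It is not assigned to the scoring of WTs.

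**The concern.** MsH scored by eye is a judgement. The rater decides whether a pause or a glance counts as seeking orientation. A rater who knows that the person is a patient, on a team that has declared patients with MCI will hesitate more, may resolve doubtful cases in that direction. Masking participants to their genotype does nothing about this, because the exposure lies with the observer.

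The scores matter to both endpoints in Section 1.7. They are part of the group comparison under the first endpoint and the dependent variables of the regression under the second. The second can be affected indirectly. If MCI participants have larger drop errors, as predicted, and are also scored with extra hesitation, a regression pooled over groups would show some association that the scorer created.

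**Working it through.** **Step 1. Which outcomes depend on an observer's judgement?**

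| Outcome | How it is obtained | Exposure to expectation |
|---|---|---|
| MsH, visual | Experimenter by eye, stopwatch and grid (2.4) | Highest |
| MsH, accelerometer | Flattened signal in 10 s windows (2.4) | Not rater-scored |
| WTs | Experimenter on a grid; defined by path taken at an intersection, overlap with Route A, or leaving usable walkways (2.4) | Lower, but no stated objective check |
| AppleGame drop error | Recorded distance (2.3.1) | None |
| Aptive gait variables | Device (text after Table 1) | None |

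Section 2.4 presents the accelerometer measure as an addition to visual scoring. It does not say which version of MsH enters the group comparison or the regression.

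**Step 2. What could the rater know?** Controls are assessed by the experimenters; SCD and MCI participants arrive from clinics (2.1). This makes control versus patient status readily known within the team. It does not show that the grid-keeper can separate SCD from MCI, since both come from the same three sites.

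**Step 3. Direction.** The declared expectation (Section 3) is more WTs and MsH in MCI, so any expectation effect would favour the hypothesis.

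**Step 4. Illustrative size.** The document gives no bias figure to reproduce, so the shifts are assumptions. Inputs:
- 25 controls and 26 MCI participants (Abstract).
- Two-sided α = 0.05 (2.4).
- A simple two-sample t-test on MsH with no true difference. This is a simplification, not the plan's stated test.
- A scoring shift of s standard deviations in MCI.

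Degrees of freedom = 25 + 26 − 2 = 49, and the critical value is 2.010. Noncentrality = s × √(25 × 26 / 51) = 3.570 × s.

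| Shift s (SD) | Noncentrality | P(false finding that MCI is worse) | P(any rejection) |
|---|---|---|---|
| 0 | 0 | 2.5% | 5.0% |
| 0.2 | 0.714 | 10.4% | 10.8% |
| 0.3 | 1.071 | 18.1% | 18.3% |
| 0.5 | 1.785 | 41.7% | 41.7% |

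The third column is the relevant one. Its baseline is 2.5%, because only one tail of the two-sided test counts as MCI being worse.

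**The case against.** The strongest reply has four parts.

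*The document does not say that the rater knows group.* A reader might infer that the scorer knows each participant's group. The text does not support that. It never says that the grid-keeper is the person who tested the controls or is told diagnoses, and the recruitment routes reveal at most control versus patient. This part stands. The point is that no rater masking is described and that control status is readily known to the team. Nor does the statement on participants and genotype imply that raters know genotype or group.

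*A journal article leaves role allocation to the full protocol.* This stands in part. Silence alone would not be a finding. Here, however, the article fixes who scores, live, with what tools and by what definition, and it does address masking, for participants only. The procedure as written is the one under review.

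*The authors added an accelerometer.* This stands as a real mitigation for MsH. It is incomplete: the visual score is kept alongside it, and the measure to be analysed is not named.

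*WTs are physical events.* Largely correct. They leave less room for judgement than MsH.

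Two further readings should be resisted. One is that the APOE prediction biases the garden scores. Section 3 states that prediction for the pure path integration subtask of the AppleGame, which is recorded as a distance, and states none for WTs or MsH. The other is that the whole first endpoint is compromised. The drop errors and gait variables are not rater-scored.

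**Conclusion.** The concern holds for visually scored MsH, and to a lesser degree for WTs. Following the plan as written, these are recorded live by the experimenter, with no masking to group described, within a team that can readily tell controls from patients and has stated the direction it expects. The bias, if present, runs towards the hypothesis.

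Its size in this study is unknown. The figures of about 10%, 18% and 42% rest on assumed shifts of 0.2, 0.3 and 0.5 SD and a simplified two-group test. They show how quickly a modest scoring tendency matters with 25 and 26 participants; they do not estimate what will happen. The conclusion does not need the rater to know every participant's diagnosis, and the document does not show that. This should be changed, but it does not undermine the machine-recorded outcomes.

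**What to change.** 1. Have the WT/MsH grid completed by a member of the staff already in the garden who did not carry out the neuropsychological assessment and is not told group.
2. Name the accelerometer-derived MsH, processed under a coded ID, as the MsH measure for the group comparison, or at least as a stated sensitivity analysis beside the visual score.
3. Check WTs against the GPX track under a coded ID without group, where GPS precision allows.
4. As a no-cost precaution, release APOE results only after the grids are locked.

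The cost is role allocation among existing staff, a hold on genotype release and some desk time to read coded tracks and signals. No participants or equipment are added. There are limits. Behaviour may still unmask some MCI participants. GPS precision in a 20 × 50 m garden is limited, and the Discussion already names GPS signal as a weakness. The accelerometer also misses spoken admissions of being unsure, so it does not replace the visual definition in full.
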